## Abstract

**Background:**

Systemic amyloidosis comprises a heterogeneous group of rare diseases characterised by extracellular deposition of misfolded protein fibrils, leading to progressive organ dysfunction. Due to the variability in clinical presentation and course, collection of system-specific and longitudinal data is essential for understanding disease progression, treatment response and patient outcomes. At the Amyloidosis Center Charité Berlin (ACCB), a prospective amyloidosis registry has been established to systematically collect clinical, laboratory, imaging and patient-reported data with the aim of improving the characterization of the diseases and facilitating translational research.

**Methods:**

This is a single-center prospective registry study that enrols patients diagnosed with systemic amyloidosis. The registry includes demographic data, multidisciplinary clinical phenotyping, biomarkers, biobanking, genetic information, imaging studies, and patient reported outcomes. Here, we describe the standardised protocol for diagnostic workup, baseline and longitudinal data collection, and disease-specific follow-up algorithms. Data will be collected digitally in interoperable data formats to ensure shareability in accordance with GDPR-policies.

**Discussion:**

This registry will serve as a resource for characterizing amyloidosis as a rare disease model in a real-world setting and identifying patterns in disease progression and treatment efficacy. By prospectively collecting high-quality longitudinal data, the study aims to generate insights that can inform clinical decision-making, improve risk stratification and support future intervention studies. In addition, the registry enables collaboration in the discovery of biomarkers and new therapeutic approaches. Ongoing analysis of this cohort will provide a basis for the further development of personalised treatment strategies and the improvement of patient care.

**Ethics and dissemination:**

Ethical approval was given by the local ethic committee. Dissemination of data in publications with different scientific observational and correlational questions is planned. **Clinical trial registration**: DRKS00032002

## Introduction

Amyloidosis enco‌‌mpasses a diver‌‌se group of rare diseases characterised by the extracellular deposition of misfolded protein fibrils, which disrupt normal tissue architecture and function [1]. The disease can affect mult‌‌iple organ systems, including the heart, kidneys, liver, nervous system, and gastrointestinal tract, leading to significant morbidity and mortality. Among the systemic forms, light-chain (AL) amyloidosis, transthyretin (ATTR) amyloidosis, and serum amyloid A (AA) amyloidosis are the most common subtypes, each with distinct pathophysiology, clinical presentation, and therapeutic considerations. Despite advances in diagnostic techniques and treatment options, amyloidosis remains a challenging condition due to its heterogeneous nature, delayed diagnosis, and limited data on long-term outcomes [2,3].

Interdisciplinary care is essential for managing rare diseases affecting multiple organ systems. Effective collaboration among specialists, primary care providers, and researchers requires seamless communication and data sharing, which can be hindered by fragmented healthcare systems and incompatible digital platforms. Differing clinical perspectives and treatment priorities can also lead to inconsistencies in patient care. Additionally, logistical barriers such as scheduling conflicts and limited access to specialised expertise may delay diagnoses and interventions. In amyloidosis, the time from first presentation until the diagnosis may take several years, especially in more unusual disease presentations [4]. Addressing these challenges require improved interoperability of health systems, standardised protocols, and integrated digital tools to enhance coordination and optimize patient outcomes. Large-scale, systematically collected clinical data are essential to improving disease characterization, understanding natural history, and optimizing treatment strategies [5]. While previous amyloidosis registries, such as the THAOS study, have provided valuable insights into disease epidemiology and prognosis [6,7], there remains a need for standardised and interoperable, continuous real-world, longitudinal data collection that reflect contemporary diagnostic and therapeutic advancements, allowing collaborative data collection between centers. Such prospective registries play a critical role in identifying prognostic markers, evaluating treatment responses, and supporting the development of personalised management approaches. In this study, we envision in depth standardization and interoperability enabling federated collaboration, expanding the potential of a single-center registry.

### Objectives

To address these gaps, we established a prospective interdisciplinary amyloidosis registry at our university hospital, aiming to systematically collect and analyse clinical, laboratory, imaging, and patient-reported outcomes from individuals diagnosed with systemic amyloidosis. This digital registry serves as a resource for both observational and translational research, fostering collaborations in biomarker discovery, disease modelling, and therapeutic innovations. For rare diseases like amyloidosis, digital registries improve data accuracy, enable real-time sharing, and support predictive models for disease progression. They also foster international collaboration, broadening our understanding of rare conditions. Our prospective registry study leverages digital innovations to collect high-quality data, advance clinical research, and improve patient care while ensuring a secure and sustainable framework for collaborative amyloidosis research. The present study describes the design, methodology, objectives and IT-specifications of this registry and provides a framework for future research and clinical applications. Importantly, this registry study incorporates individualization of data collection based on clinical care, integrating data collection smoothly into clinical care processes. Here, we roll out an example for time-efficient, care-based data collection for present and future interoperable and big-data analysis.

### Study design

This study is a single-center, observational, prospective cohort study (protocol version 1, 03.2020).

## Methods and analysis

### Study setting

The interdisciplinary Amyloidosis Registry is hosted by the Charité – Universitätsmedizin Berlin and embedded in the specialised Amyloidosis Center Charité Berlin (ACCB), which encompasses several medical specialties, including neurology, cardiology, hematology-oncology, nephrology, gastroenterology, radiology, nuclear medicine and ophthalmology. The study was approved by local ethical committee of the Charité – Universitätsmedizin Berlin and was registered under the identifier DRKS00032002 at the German Registry of Clinical Studies (DRKS – Deutsches Register Klinischer Studien). Participants are recruited via the ACCB outpatient clinic as well as from referring physicians with suspected or confirmed diagnosis of amyloidosis. Referring physicians are openly invited to present cases at the ACCB case conference (contact via [contact]) and scheduled for study inclusion and data collection in the corresponding ACCB specialty outpatient clinic. The study is purely observational and collects longitudinal data from patients with amyloidosis or suspected amyloidosis (until exclusion of amyloidosis). Primary presentation of patients with amyloidosis requires the identification of [1] organ manifestation, [2] amyloid type, and [3] therapeutic approach. Since many types of amyloidosis can affect several different organ systems, patients may present at different specialists, which can impose challenges in the structured documentation and continuation of workflow. To address this, patient cases are discussed in weekly case conferences in an interdisciplinarity fashion, always including at least one specialised cardiologist, neurologist, and hematologist, as well as a nuclear medicine specialist, and specialists depending on the respective organ manifestation of patients discussed. In the case conference, the diagnosis is either confirmed and treatment as well as follow-up procedure depending on the respective diagnosis decided, or further diagnostics and a new case conference are planned.

### Study status

Ongoing (study start: 03.04.2020; study duration: at least 10 years; end date: 03.04.2030 or later; expected completion of participant recruitment: 2030 or later, expected results from study: 2030 and earlier for sub-study results). On March 31^st^ 2026, recruitment included a total of 849 patients.

### Eligibility criteria

#### Inclusion criteria.

1. Age ≥ 18 years2. Patients with suspected or diagnosed amyloidosis (any of the below)a. Clinically suspected diagnosis resulting from imaging or laboratory parametersb. Histomorphological diagnosis of amyloidosis or positive DPD scanc. Genetically confirmed TTR mutation3. Voluntary signing of informed consent (including opt-in options for collection of biological specimens)

#### Exclusion criteria.

1. Age < 18*2.* Lack or inability for voluntary signing of informed consent

### Interdisciplinary data collection

This structure enables comprehensive patient evaluation and multidisciplinary collaboration. The registry is designed to systematically collect longitudinal clinical, laboratory, imaging, and patient-reported data.

### Ethics approval and consent to participate

The study was approved by the Ethics Committee of Charité—Universitätsmedizin Berlin (Ref. EA1/014/20). Written informed consent is obtained from all participants prior to enrolment. The consent process covers (i) the scope of data and sample collection; (ii) optional written consent for long-term biobanking (serum/EDTA plasma, aliquoted and stored) and written consent for any genetic testing relevant to amyloidosis; (iii) permission to publish de-identified aggregate results; and (iv) the right to withdraw at any time without impact on clinical care, including options for destruction of stored samples and cessation of further data use. Participants are explicitly informed that only future use of data or biospecimen collected during the study is stopped upon withdrawel, as participant records, all associated data and biospecimen will be eliminated. However, data already analysed or published cannot be removed, biological samples already distributed or used cannot be eliminated, and clinical records including results from study analyses, such as genetic findings, cannot be removed from existing medical records.

Genetic counselling is offered to all participants undergoing genetic testing; if a pathogenic variant is identified, counselling addresses implications for at-risk relatives. Incidental findings of clinical significance (imaging, genetic, or laboratory) are returned according to predefined clinical governance procedures, with appropriate referral and follow-up.

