### Biobanking

For biobanking, serum and EDTA blood samples are collected at the first visit, as well as every 12 months. Serum samples are centrifuged at 2,500 g for 10 minutes, both serum and EDTA are distributed into 250µl aliquots and stored at −80°C at the Central Biobank (ZeBanC) for up to 30 years post study inclusion. Additionally, any tissue biopsies taken are stored at the ZeBanC after written informed consent. Access to biospecimen by written request has to be individually granted by the principal investigator. Sample destruction in case of participant withdrawal is performed upon written instruction by the study team.

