### Statistical analysis plan

We prespecify the following primary endpoints: [1] overall survival from registry enrolment; [2] organ-specific progression (e.g., incident heart failure, renal failure) defined by laboratory, imaging, and electrophysiological standard clinical criteria (e.g., N-terminal pro B-type natriuretic peptide or reduction of ejection fraction in echocardiography for heart failure, creatinine clearance for renal failure, neurofilament light chains and nerve conduction studies for neuropathy progression, and further as detailed in the subtype-specific sections in the Study Protocol); and [3] longitudinal quality-of-life scores. Secondary endpoints include subtype-specific trajectories and treatment-specific outcomes. Survival endpoints will be calculated using Kaplan–Meier and Cox models; when competing risks are relevant (e.g., cause-specific events), Fine–Gray models will be used. Longitudinal continuous outcomes (biomarkers, PROMs) will be analysed with linear mixed-effects or generalised estimating equations. For comparative effectiveness questions, we will adjust for confounding using multivariable regression and propensity score methods (matching/weighting); the a priori covariate set includes age, sex, subtype, baseline stage/organ involvement, and key comorbidities (DAG-informed).

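### The withdrawal rule is inconsistent; if it erases every withdrawer's record, later overall-survival analyses can only match or exceed the mortality obtained by censoring at withdrawal

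*Protocol article*

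**What the plan says.** The section on ethics approval and consent makes three statements about withdrawal.

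- Consent item (iv) describes a right to withdraw at any time, "including options for destruction of stored samples and cessation of further data use".
- The next sentence tells participants that "only future use of data or biospecimen collected during the study is stopped upon withdrawel". It gives the reason in the same breath: such use "is stopped upon withdrawel, as participant records, all associated data and biospecimen will be eliminated".
- The sentence after that sets limits: "data already analysed or published cannot be removed". Samples already handed out or consumed, and results already in the medical record, are also exempt.

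The Biobanking section adds: "Sample destruction in case of participant withdrawal is performed upon written instruction by the study team". It does not say whether the participant has to ask. The section on study discontinuation names only exclusion of the diagnosis, so it does not help.

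The section headed Statistical analysis plan makes "overall survival from registry enrolment" the first primary endpoint and organ-specific progression the second. They are analysed by Kaplan–Meier and Cox models, with Fine–Gray models for competing risks and multiple imputation for missing data. The article does not say how withdrawn participants enter these analyses and gives no expected withdrawal rate.

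**The concern.** Options, a stop to future use only, and elimination of everything are three different rules. They have different consequences for the data.

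If elimination applies to every withdrawer, a participant who consented and was observed for several years disappears back to enrolment in any analysis run afterwards. Anyone who withdraws is alive on that day, while anyone who dies first stays in. Membership of the analysed cohort then depends on a later event. This distorts survival even when withdrawal has nothing to do with prognosis, a situation in which censoring at withdrawal would be unbiased.

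The statistical section cannot repair this later. An erased record can be neither censored nor imputed. The registry is planned for at least 10 years, with recruitment to 2030 or beyond, so withdrawals have time to accumulate.

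**Working it through.** **The plan's own precision figure.** The article states about ±6% (95% CI) for a 10% event rate at N of roughly 100–150. The Wald half-width is 1.96 × √(0.1 × 0.9 / N), which gives 5.9 points at N = 100 and 4.8 at N = 150. The figure reproduces at the lower N. It does not depend on the withdrawal rule and serves only as a yardstick. At the 849 participants reported under Study status, the same formula gives 2.0 points.

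**Overall survival, withdrawal unrelated to prognosis.** Assumptions: constant hazards over 5 years, true 5-year mortality M, and probability W of withdrawing within 5 years in the absence of death. The documents give no W, so 2–30% is shown.

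- Hazards: λ = −ln(1 − M)/5 for death and μ = −ln(1 − W)/5 for withdrawal.
- Died before withdrawing: p_d = λ/(λ + μ) × [1 − (1 − M)(1 − W)].
- Alive and not withdrawn: p_s = (1 − M)(1 − W).
- Mortality after erasure: p_d/(p_d + p_s).

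Example with M = W = 10%: λ = μ, so p_d = 0.5 × (1 − 0.81) = 0.095 and p_s = 0.81. The result is 0.095/0.905 = 10.5%.

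Example with M = 50%, W = 30%: λ/(λ + μ) = 0.6931/(0.6931 + 0.3567) = 0.660, p_d = 0.660 × 0.65 = 0.429 and p_s = 0.35. The result is 0.429/0.779 = 55.1%.

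Apparent 5-year mortality after erasure:

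| True mortality | W = 2% | 5% | 10% | 20% | 30% |
|---|---|---|---|---|---|
| 10% | 10.1% | 10.2% | 10.5% | 11.1% | 11.8% |
| 30% | 30.2% | 30.6% | 31.2% | 32.6% | 34.2% |
| 50% | 50.3% | 50.7% | 51.5% | 53.2% | 55.1% |

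Censoring at withdrawal returns the true value in every cell.

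**Overall survival, withdrawal related to prognosis.** This was simulated with 400,000 participants. Half had 0.5 times and half 1.5 times the base death hazard, and base withdrawal was 20%. In the related scenarios the withdrawal hazard was 1.8 times base in one half and 0.2 times base in the other.

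| Who withdraws | True | Censored | Erased |
|---|---|---|---|
| Unrelated to prognosis | 28.9% | 28.9% | 31.5% |
| Mostly sicker | 29.0% | 27.9% | 30.0% |
| Mostly healthier | 28.8% | 30.0% | 32.5% |

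Erasure exceeds censoring in each row. Its distance from the truth depends on who leaves.

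**Organ progression.** A participant can progress and then withdraw, so erasure removes events as well as event-free time. This was simulated with a 5-year progression risk of about 30% and base withdrawal of 20%, leaving death out.

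| Withdrawal rate after progression | Censored | Erased |
|---|---|---|
| Unchanged | 29.9% | 29.9% |
| 3 times higher | 30.0% | 25.4% |
| 6 times higher | 30.0% | 19.9% |

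**The case against.** The sentence can be read coherently: the record is removed from the withdrawal date onward, while past analyses stand. The options in item (iv), and the written instruction in the Biobanking section, suggest that a choice may already exist. The consent form and full protocol are not shown. The study has ethics approval and participants are told of the elimination, so this is partly a consent policy and not only a statistical one. Formal withdrawal may also be rare; nothing in the clause erases participants who are merely lost to follow-up. At the plan's own 10% event rate the excess stays below the stated ±6 points even at 30% withdrawal. When sicker participants leave, censoring errs by about as much as erasure, in the other direction (27.9% and 30.0% against 29.0%).

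Much of this stands. It rules out the claim that every record is certainly erased, and it keeps the point modest. It does not remove the point. The elimination clause is a stated rule, not a detail left to another document, and it is irreversible once applied. Bias also does not shrink as the registry grows, and recruitment is already well beyond the N behind the ±6 points.

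Three stronger inferences are tempting but unsupported:

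- **Progression is overstated too.** The simulation shows no bias or understatement.
- **Earlier sub-study results could not be reproduced.** Data already analysed are exempt, and the article does not say whether analysis datasets are archived.
- **Withdrawals could not be counted.** The article does not say that no tally is kept, and it describes audit logs and trackable changes.

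**Conclusion.** The withdrawal text is inconsistent and should be reconciled. If elimination is applied to every withdrawer, later overall-survival estimates show mortality equal to or above the estimate with censoring at withdrawal. That direction follows from logic alone.

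The size rests on assumed withdrawal rates, constant hazards and withdrawal unrelated to prognosis. At 2–10% withdrawal over 5 years the excess is about 0.1–0.5 points at 10% true mortality and 0.3–1.5 points at 50%. At 30% withdrawal it is about 1.8–5.1 points. A reader might conclude that mortality is simply overstated by the plan. The documents do not support that, because they leave open whether erasure is automatic, give no withdrawal rate, and cannot show whether withdrawal is related to prognosis.

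For organ progression no direction can be stated in advance. This is a worthwhile and inexpensive correction, not a flaw that invalidates the registry.

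**What to change.** Reconcile the ethics section and the Biobanking section so that both describe the same choice at withdrawal:

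- **(a)** No new data or samples are collected. Data up to the withdrawal date are kept and the participant is censored on that date.
- **(b)** Data are fully erased and samples destroyed, at the participant's request.

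Use the new wording for new participants. Offer the choice at the time of withdrawal to those enrolled under the current wording, so that no existing promise is weakened.

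For (b), keep a non-identifying count by subtype and time since enrolment, where the cells are large enough to stay anonymous, and report it with the results. Add a bounding sensitivity analysis for overall survival, for example treating all erased participants as alive to the horizon and then as dying just after withdrawal.

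The cost is a consent wording change, notification of the ethics committee and a small log. The right to erasure is untouched. Censoring under (a) still assumes that withdrawal is unrelated to prognosis, but with the data kept, withdrawers' characteristics up to that date can be examined.

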### Study Protocol

This study aims at understanding real-world disease course, treatment effects, and quality of life of patients affected with systemic amyloidosis in an interdisciplinary setting. In order to achieve a broad understanding of organ involvement and outcomes, system-specific outcome measures were chosen to record longitudinal patient data dependent on organ involvement. For each specialty, we defined a standardised dataset to enable research and further collaboration efforts depending on the diagnosis. Although patients may present at any discipline when amyloidosis is first suspected, all patients undergo detailed cardiology and neurology examinations. Within the cardiology and neurology departments, informed written consent is obtained, and patients are enrolled in the registry study using a web-based database (Tbase) [8], that has been modified to reflect the needs of the ACCB. Tbase has been established, facilitating the easy entry of key data. This includes basic information such as demographics, height, weight, (suspected) diagnosis, (primary) organ manifestation, and therapy. Additionally, structured medical history and examination data are documented digitally and numerically to enable structured data analysis. Laboratory, imaging, and other ancillary data are automatically integrated from the hospital information system. Fig 1 presents an overview of enrolment and study visits.

**Fig 1 pone.0350084.g001:**
[figure not shown]
SPIRIT schedule. No interventions are planned as this is a purely observatory study. Timepoints as depicted as t1-t4, etc. are defined in respective figures (as stated in left column) depending on baseline disease. Assessment datasets are defined in Figs 2-8. Core datasets are indicated as X; extended datasets are indicated by the symbol **(x)**.

### Baseline data collection ATTR amyloidosis

Patient with suspected ATTR amyloidosis always undergo cardiological, neurological, and genetic examinations. As depicted in Fig 2, neurological examination includes detailed cognitive, sensory, and motor examinations with quantification using the Neuropathy Impairment Score (NIS). Nerve conduction studies (NCS), electromyography (EMG), and sensory evoked potentials are performed for baseline definition of neuropathy or dysfunction of central conduction due to, i.e., spinal canal sten‌‌osis. Further examination of affection of the central nervous system is performed depending on the patient’s symptoms as well as the underlying genotype (in case of hereditary ATTR (ATTRv) amyloidosis). Likewise, biopsies are only performed in specific cases, e.g., variants of unknown significance (VUS) and uncertainty regarding the affection of the peripheral nervous system. The basic cardiological examinations include a medical history, symptoms according to the New York Heart Association definition (NYHA stage), an electrocardiogram (ECG), transthoracic echocardiography including strain analysis. All patients receive a clinical examination (including additional tests such as the 6-minute-walk-test in selected cases), blood pressure measurement, and a technetium-99m (99mTc) and 3,3-diphosphono-1,2-propandicarboxylic acid (DPD) scan. If high free serum light chains or monoclonal gammopathy of unclear significance (MGUS) are detected or in the case of non-conclusive findings, a biopsy of an involved organ is performed. Cardiac magnetic resonance imaging (CMR) including cine imaging, parametric mapping and late Gd enhancement assessment is also performed in selected cases. CMR is evaluated in a core laboratory setting blinded for clinical information. Laboratory profiles are taken either during cardiology or neurology visits and include parameters of cardiac, renal, hepatic function, as well as parameters to detect important differential diagnoses for peripheral neuropathies such as long-term blood sugars and vitamins. Likewise, genetic testing is performed in all patients with suspected ATTR amyloidosis after written informed consent. Genetic counselling in case of detection of TTR mutation also includes discussion of testing of unaffected first-degree family members and VUS. Unless clearly identified as benign from the literature, patients carrying VUS are included in the same observational examinations as patients carrying pathogenic mutations. Depending on organ manifestation, individual symptoms, and genetic variant, all (potentially) affected organ systems are systematically examined as depicted in Fig 2, right side. Ophthalmologic examination includes refraction, visual acuity, intraocular pressure, examination of anterior and posterior compartments, as well as optical coherence tomography. Nephrological examination includes expanded laboratory testing, while biopsies are only performed in cases with unclear renal involvement or concurring etiologies. Gastroenterological testing includes questionnaires for autonomous function, as well as endoscopy in cases of severe involvement, including deep colon biopsies for proof of amyloid depositions. Hematological testing includes interpretation of laboratory findings in case of detection of an MGUS and performing a bone marrow biopsy for detection of amyloidosis and for diagnosis of plasma cell dyscrasias.
